### Strategies to improve adherence to interventions {11c}

SIMPLIFIED has been designed as a pragmatic trial, and as such cholecalciferol will not require trial-specific dispensing, labelling or accountability records. However, it is anticipated that the majority of patients enrolled in the trial will be receiving in-centre haemodialysis, and cholecalciferol will be administered as part of the dialysis prescription where possible, and hence will be supervised.

Plasma vitamin D levels will also be measured during the first year of the trial. Samples will be taken 4 months (collected in a window of −1 week and + 5 weeks) after the baseline visit for the first 230 patients enrolled into the trial to ensure that there is separation in levels between the cholecalciferol and control groups.

### Relevant concomitant care permitted or prohibited during the trial {11d}

With the exception of cholecalciferol or ergocalciferol, there is no contra-indicated concomitant therapy. Patients randomised to the cholecalciferol group, whose standard care already involves the administration of low-dose cholecalciferol or ergocalciferol (≤ 1000 IU/day), must discontinue these medications upon randomisation to the cholecalciferol group and prior to the administration of the first trial dose.

All patients will be permitted to continue treatment with any active (1α-hydroxylated) compounds, including alfacalcidol, calcitriol, paricalcitol and 22-oxacalcitriol. It is anticipated that cholecalciferol 60,000 IU fortnightly will reduce or remove the requirement for active vitamin D. Therefore, prescriptions for active vitamin D preparations should be assessed regularly along with routine dialysis reviews as per local policy whilst patients are enrolled in the trial.

### Provisions for post-trial care {30}

Should this intervention improve patient survival, cholecalciferol is a low-cost, easy to administer therapy, and it is anticipated that it could be rapidly rolled out to the UK dialysis population. For participants, whilst in the trial, Cambridge University Hospitals NHS Foundation Trust, as a member of the NHS Clinical Negligence Scheme for Trusts, will accept full financial liability for harm caused to participants in the clinical trial caused through the negligence of its employees and honorary contract holders. There are no specific arrangements for compensation should a participant be harmed through participation in the trial, if no-one has acted negligently. The University of Cambridge will arrange insurance for negligent harm caused as a result of protocol design and for non-negligent harm arising through participation in the clinical trial.

### Outcomes {12}

#### Primary outcome measure

The primary outcome is all-cause mortality. Deaths will be captured from Office National Statistics (ONS) datasets.

#### Secondary outcome measures

Health-related quality of life assessed by EQ-5D-5LComposite cardiovascular events defined as cardiovascular death, acute coronary syndrome (ACS), heart failure, cardiac arrhythmia admissions and stroke requiring hospital admission from Hospital Episode Statistics (HES) data*Infections requiring hospital admission from HES data*Cancer incidenceFractures requiring hospital admission from HES data*Cost-effectiveness of cholecalciferol from the perspective of the NHS

*The statistical analysis plan will contain lists of specific HES codes which constitute each of the secondary endpoints.

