**Methods:**

The SIMPLIFIED (Survival Improvement with Cholecalciferol in Patients on Dialysis) trial will test whether supplementation with high-dose cholecalciferol improves survival. Adult dialysis patients will be recruited from one of 72 UK renal centres, by local clinicians and research nurses, and randomly assigned in a 1:1 ratio to high-dose open-label cholecalciferol or standard care, stratified by site. Trial outcomes will be captured using existing data sources including Office of National Statistics (ONS) for deaths and Hospital Episode Statistics (HES) for secondary endpoints. The primary endpoint of the trial is all-cause mortality. Key secondary endpoints include survival free from cardiovascular events, infections and cancers, and quality of life and cost-effectiveness measures utilising the Eq5D tool. Severe adverse event line listings will be generated from HES data for safety reporting. In this superiority trial, it is anticipated that approximately 4200 patients in total will need to be enrolled to observe 2200 deaths over a period of about 7 years, which will yield 90% power to demonstrate a hazard ratio of 0.87.

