#### Secondary objectives

To determine the effect of cholecalciferol (60,000 IU fortnightly) on hospital admissions due to cardiovascular events, infections or fracture, cancer incidence, quality of life and evaluate the cost-effectiveness of cholecalciferol from the perspective of the NHS.

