#### Secondary outcome analyses

Secondary assessments will evaluate the effect of cholecalciferol on quality of life using EQ-5D-5L data. Intention-to-treat analyses on the effect of randomisation to cholecalciferol on infections requiring admission, incidence of malignancy, fracture requiring admission and hospitalisation with cardiovascular events including atherosclerotic events, arrhythmias, heart failure and stroke will be carried out. Analysis of the time to first non-atherosclerotic cardiovascular event will be assessed.

Relevant secondary endpoints will be assessed using time to event analysis (Cox proportional hazards regression modelling). Time to event data will be summarised using Kaplan–Meier curves. Events that may occur multiple times (acute coronary syndrome, fracture) will be analysed using repeated events analysis. The treatment effect for secondary endpoints will be reported using point estimates, with nominal 95% confidence intervals and *p* values.

Cost-effectiveness will be gauged using a cost-effectiveness analysis (CEA) and cost-utility analysis (CUA). For both, the costing perspective will be that of the NHS (specifically that of secondary care—restricted to this perspective as resource data is only collected from Hospital Episode Statistics (HES) and related sources). In the CEA, outcomes will be compared in terms of life years gained (related to the primary outcome). For the CUA, outcomes will be compared using quality adjusted life years, calculated from EQ-5D-5L. For both analyses, a range of time frames (time horizons) will be considered, starting from a year and then at subsequent years for the range available within the data.

The overall conclusions of the study in terms of formal inference to reject or retain the null hypotheses associated with each endpoint will explicitly account for multiple testing to restrict the family-wise error rate (the overall chance of one or more type I errors) to below 5%.

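### The cardiovascular secondary endpoint counts cardiovascular death in the outcome list, omits it from the objectives and the analysis section, and counts any death in the abstract

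*Protocol article*

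**What the plan says.** The protocol describes the cardiovascular endpoint in four places.

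- **Abstract, Methods:** "Key secondary endpoints include survival free from cardiovascular events, infections and cancers". On the ordinary meaning of event-free survival, a death from any cause is an event.
- **Secondary objectives {7}:** "hospital admissions due to cardiovascular events, infections or fracture, cancer incidence". Cardiovascular death is not mentioned.
- **Secondary outcome measures {12}:** "cardiovascular events defined as cardiovascular death, acute coronary syndrome (ACS), heart failure, cardiac arrhythmia admissions", with stroke admissions completing the list. Cardiovascular death is a component.
- **Secondary outcome analyses {20a}:** intention-to-treat analyses of several outcomes, the cardiovascular one being "hospitalisation with cardiovascular events including atherosclerotic events, arrhythmias, heart failure and stroke will be carried out". Cardiovascular death is again absent. The section then adds: "Analysis of the time to first non-atherosclerotic cardiovascular event will be assessed". That analysis is not in the outcome list.

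The data-source sections follow the admissions-only version. The consent provisions {26b} pair primary and secondary endpoints with deaths and hospital admissions respectively. The participant timeline {13} and the outcome collection plan {18a} take secondary endpoints from Hospital Episode Statistics (HES) or its equivalents.

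The analysis section names Cox regression and Kaplan-Meier curves for the time-to-event secondary endpoints. It promises formal inference on each endpoint with the family-wise error rate held below 5%.

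**The concern.** All deaths, cardiovascular deaths and no deaths give three event sets and three null hypotheses. The protocol leaves the lists of HES codes to the statistical analysis plan, but a code list does not decide which deaths are events. This is therefore a conflict between statements in the document, not a detail left for later.

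Two things are at stake. A cardiovascular death outside hospital is an event in the outcome list and is lost in an analysis of admissions. Error control across endpoints also needs one fixed hypothesis per endpoint, and this endpoint has more than one.

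**Working it through.** **1. Event sets side by side**

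| Endpoint | Abstract | Objectives | Outcome list | Analysis section |
|---|---|---|---|---|
| Cardiovascular | any death or event | admissions | admissions and cardiovascular death | admissions |
| Infection | any death or event | admissions | admissions | admissions |
| Cancer | any death or event | incidence | incidence | incidence |
| Fracture | not named | admissions | admissions | admissions |

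Only the cardiovascular row conflicts outside the abstract.

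**2. The plan's own figure**

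The sample size section {14} gives 2200 deaths, 90% power, two-sided 5% and hazard ratio 0.87. The Schoenfeld formula, 4(1.960 + 1.282)² / (ln 0.87)², needs 2168 deaths and Freedman's needs 2175. Power with 2200 deaths is 90.4%. The primary calculation reproduces and is not in question. No power is stated for any secondary endpoint.

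**3. Inputs for the comparison**

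- Control death hazard from 68% three-year survival {14}, taken as exponential: λ = -ln(0.68)/3 = 0.1286 per year.
- Hazard ratio 0.87 on every kind of death and 1 on non-fatal events.
- Assumed, since the protocol gives no figures: cardiovascular admission rate a = 0.10 to 0.20 per year; cardiovascular share of deaths s = 0.2 to 0.4.

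**4. Cardiovascular hazard ratio under each version**

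- Event-free survival, (0.87λ + a)/(λ + a): a = 0.10 gives 0.2118/0.2286 = 0.927; a = 0.20 gives 0.3118/0.3286 = 0.949.
- Composite, (0.87sλ + a)/(sλ + a): s = 0.4, a = 0.10 gives 0.1447/0.1514 = 0.956; s = 0.2, a = 0.20 gives 0.2224/0.2257 = 0.985.
- Admissions only, censoring at death: a/a = 1.00.

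The composite formula adds every cardiovascular death to the admissions. Data management {19} counts all diagnoses within an inpatient spell, so a death during an admission with a qualifying code has already been counted at that admission. The gap between composite and admissions is therefore at the large end here.

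**5. Chance of a nominally significant result**

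Assume 4200 patients, uniform accrual over 4 years and 7 years in total. Event-free survival then has 2756 first events at a = 0.10 and 3293 at a = 0.20. The chance of p < 0.05 is 51% and 32%. With admissions only it is the nominal 5%, because the hazard ratio is 1.

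**6. The abstract's wording applied to cancer and infection**

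Put an assumed event rate c in place of a in the event-free survival formula.

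- Cancer, c = 0.01 to 0.05: 0.1218/0.1386 = 0.879 up to 0.1618/0.1786 = 0.906. The chance of nominal significance is 82% down to 67%.
- Infection admission, c = 0.05 to 0.50: 0.906 up to 0.973. The chance is 67% down to 13%.

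Under the incidence or admission definitions the cause-specific hazard ratio is 1.00 throughout.

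**The case against.** A reader might infer that all the key secondary endpoints are defined three ways, so that a mortality effect would be reported as a cancer or infection benefit. The protocol does not support that. Infection, cancer and fracture each keep one meaning across objectives, outcome list and analysis. The event-free survival wording is a single clause in an abstract, which condenses, and it could even be read as one combined outcome. No section of the methods plans a cancer-free or infection-free survival analysis. The figures in step 6 apply only if the abstract's wording is what is analysed or reported.

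A reader might also infer that, because the trial is open-label, the definition could be picked after seeing the results. The blinding section {17a} restricts aggregate statistics by arm to the data monitoring committee, so the protocol gives no ground for that before the final analysis.

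Other points on that side carry weight. The gap between the composite and admissions only is small. The statistical analysis plan, which is not shown, may settle which deaths count. The non-atherosclerotic analysis looks like part of a composite that already contains heart failure and arrhythmia, and its place in the error-controlled family is something an analysis plan commonly decides.

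The direct conflict over cardiovascular death between the outcome list and the objectives and analysis section remains. The abstract's wording still differs from both.

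**Conclusion.** The concern holds for the cardiovascular endpoint. Its event set differs between sections, and the choice moves the hazard ratio from about 0.93-0.95 through 0.96-0.99 to 1.00 if the treatment affects mortality alone. Those values rest on constant hazards, a common effect on all deaths, and assumed admission rates and cardiovascular share of deaths. The 1.00 also assumes a cause-specific Cox model.

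For cancer and infection the point is limited to correcting the abstract. It is worth making because reporting cancer under that wording could show a mortality effect as a cancer benefit, with a hazard ratio of about 0.88-0.91 at 1-5% per year. The primary endpoint is unaffected. The definitions should be reconciled before data lock.

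**What to change.** 1. Take the list under Secondary outcome measures as the single definition of each endpoint.
2. In Secondary outcome analyses, analyse time to the first event of the cardiovascular composite, including cardiovascular death from the Office for National Statistics death data already obtained for the primary outcome. Confirm that the extract carries cause of death, which the protocol does not state.
3. Add cardiovascular death to the secondary objective, and replace the event-free survival phrase in the abstract with the listed endpoints.
4. Treat deaths that are not part of an endpoint as competing events: cause-specific hazard ratios, with cumulative incidence curves in place of Kaplan-Meier curves for the non-fatal endpoints. The planned repeated-events analyses of acute coronary syndrome and fracture are not affected by the change of definition.
5. State whether the non-atherosclerotic analysis belongs to the error-controlled family.

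The cost is wording changes and a little extra analysis work before data lock, with no new data collection if cause of death is in the extract.

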### Participant timeline {13}

SIMPLIFIED is a pragmatic trial designed to exploit existing data sources to maximise efficiency and minimise research cost. As such no dedicated study visits outside of routine care are planned (Fig. 3). Many variables often captured face to face or during trial visits will be captured indirectly using a variety of routinely collected data sources. Data on the primary endpoint (death) will be captured via regular data tranches from Office of National Statistics (ONS). Data on secondary endpoints will be captured using Hospital Episode Statistics (HES) data downloads (or equivalent in Scotland and Wales), obtained regularly for the trial population. Laboratory data will be obtained from the results of routinely collected blood tests via the UK Renal Registry (UKRR) on an on-going basis. Calcium and phosphate concentrations are measured regularly in all UK dialysis patients as part of standard care, and these data are already submitted to the UKRR. Monitoring for hypercalcaemia will be driven by routine clinical practice and management based on local hypercalcaemia guidelines and practices.

**Fig. 3 Fig3:**
[figure not shown]
Assessment schedule. *Eq5D data collection ceased in April 2023. QoL, quality of life; SAR, serious adverse reaction; SUSAR, suspected unexpected serious adverse event; HES, Hospital Episode Statistics; ONS, Office of National Statistics; UKKR, UK Renal Registry; SAIL, Secure Anonymised Information Linkage; eDRIS, Electronic Data Research and Innovation Service

### Sample size {14}

The SIMPLIFIED study is an event-driven trial. It is estimated that the control arm has a 3-year survival of 68% [1]. It is estimated that randomisation of 4200 patients would yield 2200 primary outcome events (deaths) over 7–8.5 years, resulting in 90% power at 5% significance (two-sided) assuming a hazard ratio of 0.87. Dropout is assumed to be negligible given the national death registry data source for primary endpoint collection.

### Recruitment {15}

SIMPLIFIED is a pragmatic, registry-facilitated study with broad inclusion criteria and limited exclusion criteria to facilitate recruitment of 4200 patients requiring dialysis and ensure that results are applicable to the general dialysis population. There are 72 renal units in the UK and it is anticipated that SIMPLIFIED will recruit from up to 65 of these. In September 2021, ethical approval was granted to enable patients to be approached and consented remotely. This measure was introduced in response to the COVID-19 pandemic which restricted movement of research nurses to satellite dialysis units, and also to encourage patients who receive dialysis outside of a unit, such as those receiving home haemodialysis or peritoneal dialysis, who are underrepresented in dialysis trials to enrol.

## Assignment of interventions: allocation

### Sequence generation {16a}

Patients will be randomised to the cholecalciferol treatment group or control group in a 1:1 ratio using a central computerised randomisation system.

### Concealment mechanism {16b}

This is an open-label study. Immediate allocation of treatment will be performed, with documentation of the decision in a confirmatory email automatically generated by the randomisation system.

### Implementation {16c}

Eligible participants will be randomised by local investigators using the web-based randomisation system embedded within the bespoke trial database, hosted by University of Cambridge. Blocked randomisation using a random block size of either 2 or 4, stratified by site, will be used. The randomisation is open-label, so the treatment assigned will be given explicitly and not blinded in any way.

## Assignment of interventions: blinding

### Who will be blinded {17a}

This is an open-label trial with patients and investigators aware of treatment allocation at an individual patient level. However, aggregate statistics broken down by treatment arms are only available to the IDMC.

### Procedure for unblinding if needed {17b}

Unblinding is not required as this is an open-label study.

## Data collection and management

### Plans for assessment and collection of outcomes {18a}

SIMPLIFIED is a pragmatic trial designed to exploit existing data sources to maximise efficiency and minimise research cost. Aside from a single baseline visit, when data is entered into an eCRF, no dedicated study visits outside of routine care are planned.

In the SIMPLIFIED trial, many variables often captured face to face or during trial visits will be captured indirectly using a variety of data sources including Office for National Statistics (ONS) for the primary endpoint death, Hospital Episode Statistics (HES) or equivalents in Scotland and Wales for secondary endpoints including cardiovascular events, severe infections and fractures, and the UK Renal Registry (UKRR) for biochemical data, such as calcium levels, which are collected and submitted to the UKRR as part of routine care. In order to evaluate the impact of the intervention on quality of life, 6-monthly EQ-5D questionnaires will be completed by participants either via a telephone call with the central study team in Cambridge, using a smartphone/web portal interface, or on paper via the post. Trial participants will provide explicit consent to the use of patient identifiable data for the purposes of the conduct of the trial. Patient identifiable data will be stored separately from anonymised trial data on a secure server hosted within University of Cambridge.

### Plans to promote participant retention and complete follow-up {18b}

SIMPLIFIED was designed to place minimal burden on participants, recognising the significant impact that dialysis already has on patients’ life, with the intention of promoting retention throughout the trial. However, it is important to collect the impact of cholecalciferol on quality of life, and therefore patients were offered the option of receiving 6-monthly EQ-5D questionnaires through the post, a smartphone/web EQ-5D data entry portal or to complete them via a telephone call with support from central study staff. For those patients who withdraw from their randomised treatment allocation in the trial, they are asked to consent to ongoing long-term follow-up via collection of routinely collected data which does not place any burden on them but provides valuable information on the long-term impact of the intervention.

### Data management {19}

Baseline data will be entered at site into an eCRF. Logical checks have been incorporated into each data field to minimise erroneous data entry. All trial data in the eCRF must be extracted from and be consistent with the relevant source documents. All subsequent data will be collected centrally. EQ-5D questionnaires will be delivered by central study staff either via telephone or post, and results entered directly into the study database, or by participants directly entering responses to EQ-5D questions via a smartphone/web interface linked directly with the study database. Data to capture all other endpoints including deaths and hospitalisations will require periodic uploads of the trial cohort to NHS England and equivalents in the devolved nations. Data received on deaths from ONS and hospitalisations from HES will be received into a secure data hosting area, processed and analysed in conjunction with study data collected via the more conventional methods. To identify patients in whom events have occurred, ICD-10 codes within HES will be flagged to identify subjects who have experienced an event (such as myocardial infarction, heart failure, stroke). A detailed description of relevant ICD-10 codes and classification will be included as an appendix in the statistical analysis plan. All diagnoses captured during a continuous inpatient spell will be considered, ensuring that relevant events are captured even if not the primary reason for hospital admission.

Prior to the primary analysis, survival status will be confirmed by cross-referencing UKRR and ONS data. For participants where no death has been recorded by either ONS or the UKRR at the end of the trial, follow-up time will be censored at the point of last known follow-up. Last known follow-up will be defined as whichever is most recent of either the date of last recorded UKRR-submitted dialysis results or last 6-monthly questionnaire follow-up. Data will be archived for a period of 5 years following the end of trial sponsor declaration.

